# Comparison between breath stacking technique associated with expiratory muscle training and breath stacking technique in amyotrophic lateral sclerosis patients: Protocol for randomized single blind trial

**DOI:** 10.1016/j.conctc.2020.100647

**Published:** 2020-09-02

**Keywords:** Amyotrophic lateral sclerosis, Assisted coughing, Breathing exercises

## Abstract

**Introduction:**

Amyotrophic lateral sclerosis (ALS) is a progressive neurodegenerative disease affecting both upper and lower motor neurons, and lead to respiratory failure. Strategies are suggested to respiratory management in ALS patients, as the breath stacking and Expiratory muscle training (EMT), which have been used as aid to assist cough in neuromuscular disorders. However, the randomized controlled trials performed in ALS patients have not investigated the addiction of EMT together breath stacking in this population. This trial aims to determine if breath stacking plus EMT is more effective than breath stacking alone to decrease the decline rate on the inspiratory/expiratory muscle strength, FVC and voluntary PCF in ALS patients.

**Methods:**

This parallel-group, assessor-blinded randomized controlled trial, powered for superiority, aims to assess pulmonary function, respiratory muscle strength, peak cough flow as primary outcomes. Forty-two participants are being recruited referral neuromuscular disease center at Brasilia, Brazil. Following baseline testing, participants are randomized using concealed allocation, to receive either: a) breath stacking technique alone or b) breath stacking technique plus EMT.

**Conclusion:**

There is a lack of evidence regarding the benefit of EMT plus breath stacking in ALS patients. This trial will contribute to evidence currently being generated in national and international trials by implementing and evaluating a respiratory therapy program including two components not yet combined in previous research, for people with ALS involving longer-term follow-up of outcomes. This trial is ongoing and currently recruiting.

**Trial registration:**

This trial was prospectively registered on the Clinical Trials Registry NCT04226144.

## Introduction

1

Amyotrophic lateral sclerosis (ALS) is a progressive neurodegenerative disease affecting both upper and lower motor neurons, which leads to a loss of voluntary muscle control [1]. As the disease progresses, muscles of respiration are affected, leading to chronic respiratory failure [2]. Respiratory failure is primarily due to respiratory muscle weakness, leading ALS patients to cough impairment, one of the main causes of hospitalization [3,4]. Producing an effective cough initially requires taking a deep breath with the inspiratory muscles, followed by maximum contraction of the expiratory muscles, with glottis closure and subsequent opening using the oropharyngeal muscles, generating an expiratory flow due to contraction of expiratory muscles capable of eliminating secretions [5,6]. This represents the inspiratory, compression and expiratory phases of cough production. Thus, strategies to enhance effective cough and lung recruitment should be recommended in ALS patients [7].

Among these strategies suggested for respiratory management in ALS patients, breath stacking has been used to assist cough in neuromuscular disorders [8]. The breath-stacking technique uses a manual resuscitation bag with one-way valve to deliver large breath volumes to the patient via a suitable interface [9]. Periodic lung expansion by breath stacking decreases basal atelectasis, and maintains compliance of the lungs and chest wall, with increases of Peak cough flow (PCF) and cough effectiveness [5]. Rafiq et al. have demonstrated that breath stacking should be recommended as a first line intervention for lung recruitment and cough augmentation in ALS patients, with no differences between breath stacking and mechanical insufflator-exsufflator for survival, quality of life and hospitalization [9].

Expiratory muscle training (EMT) has been investigated as a new effective tool to enhance maximal PCF in individuals with neuromuscular diseases. This technique aims to improve subglottic air pressure generation, swallowing and airway clearance [10]. Reyes et al. have shown that EMT plus breath stacking improved voluntary and reflex cough in Parkinson disease [11]. Plowman et al. have demonstrated that 5-week EMT training was feasible and led to improvements in respiratory and bulbar function in ALS patients [10,12]. However, both studies have not used the techniques together, which may improve the clinical results. Of note, the randomized controlled trials performed in ALS patients have not investigated the addiction of EMT together breath stacking in this population.

This trial aims to determine if breath stacking plus EMT is more effective than breath stacking alone to decrease the decline rate on the inspiratory/expiratory muscle strength, pulmonary function testing and voluntary PCF in ALS patients. We hypothesize that those receiving breath stacking plus EMT will have a slower decline in these parameters from baseline to 6 months, compared to patients that receiving breath stacking alone. The key secondary outcomes are to assess whether EMT plus breath stacking is superior to breath stacking alone to swallowing function and ability to speech. This protocol is reported according to the Standard Protocol Items: Recommendations for interventional Trials (SPIRIT guidance) [13].

### Methods/design

1.1

This two-arm, parallel (1:1), superiority, blinded-assessor, randomized controlled trial is being conducted at referral neuromuscular disease center in Brasilia, Brazil. This trial has been prospectively registered on Clinical Trials Registry (NCT04226144). Recruitment commenced in August 2019.

### Participants

1.2

Fig. 1 outlines participants’ flow through the study. Eligible participants are identified through screening at the neuromuscular disease center. To be eligible, participants must have a diagnosis of neuromuscular disease confirmed by neurologists at the referral center for neuromuscular diseases in Brasília prior to screening for recruitment. Other eligibility requirements are: age over 18 years; preserved cognition, as evidenced by a score greater than or equal to 24 points in the Mini-Mental Status Exam; no barium allergies; without tracheostomy or invasive mechanical ventilation; no diaphragmatic pacemaker; and no associated respiratory disease. Participants are excluded if they are pregnant; had previous kidney disease or other concomitant diseases; had respiratory diseases; or are hospitalized in intensive care units (ICUs) during the study.

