##### Bulbar function

1.4.4.3

Bulbar function will be assessed using the three components of the revised ALS functional rating scale (ALSFRS-R) relevant to bulbar function (i.e. speech, salivation and swallowing, each scored on a scale of 0–4).

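### The only diagnostic entry criterion is any neuromuscular disease, although the trial's title, aim and conclusions concern ALS alone

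*Protocol article*

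**What the plan says.** **Eligibility.** Section 1.2 (Participants) states that "participants must have a diagnosis of neuromuscular disease confirmed by neurologists" at the Brasília referral centre. The source of patients is equally broad: "Eligible participants are identified through screening at the neuromuscular disease center". The remaining inclusion items concern age, cognition and barium allergy, followed by "without tracheostomy or invasive mechanical ventilation; no diaphragmatic pacemaker; and no associated respiratory disease". The exclusions concern pregnancy, kidney, concomitant and respiratory disease, and intensive care admission. ALS is not mentioned in this section.

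**Target population.** The title ends "breath stacking technique in amyotrophic lateral sclerosis patients: Protocol for randomized single blind trial". The Abstract gives the aim as slowing the "decline rate on the inspiratory/expiratory muscle strength, FVC and voluntary PCF in ALS patients". The Introduction repeats the aim for "pulmonary function testing and voluntary PCF in ALS patients" and states the hypothesis of slower decline over six months. The conclusions of the Abstract and of section 3 speak of people with ALS.

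**Data collected.** Section 1.4.4.3 (Bulbar function) uses three components of the "revised ALS functional rating scale (ALSFRS-R) relevant to bulbar function". Section 1.4.4.4 (Secondary outcomes) records the total score on the same scale and the months from first symptoms to the diagnosis of ALS.

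**The concern.** An eligibility criterion is an operational rule: whoever screens patients applies it as written. This one describes a wider population than the question the trial asks.

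Two things are at stake. The first is interpretation. If patients with other neuromuscular diseases were randomised, the treatment comparison would be an average over a mixture, and the ALS-specific claims in the Abstract and section 3 would not follow from it. The second is sensitivity. The hypothesis is that the added training slows decline. Patients in whom there is no treatment difference in decline would pull the average difference towards zero, and with 16 patients per arm there is little room for that. The documents establish the first directly. The second depends on assumptions that they do not supply.

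**Working it through.** **Step 1. Does any other item restrict entry to ALS?**

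| Item in section 1.2 | Restricts to ALS? |
|---|---|
| Confirmed neuromuscular disease | No, broader class |
| Age, cognition score, barium allergy | No |
| Tracheostomy or invasive ventilation, diaphragmatic pacemaker | No |
| Respiratory disease (listed as both a requirement and an exclusion) | No |
| Pregnancy, kidney or other concomitant disease, intensive care | No; these do not bear on the primary neuromuscular diagnosis |
| Screening at the neuromuscular centre | No |

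**Step 2. Does the article use the two terms as synonyms?** It does not. The Introduction presents breath stacking as a cough aid in neuromuscular disorders generally and then turns to ALS. Its paragraph on expiratory training opens with neuromuscular diseases as a class and then discusses Parkinson disease and ALS separately. The criterion therefore cannot be read as another name for ALS.

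**Step 3. The plan's own figures.** Section 1.5 gives 16 per arm, 80% power, two-sided 5%, an important difference of 2–6% of predicted FVC over one year, and 42 in total after 30% attrition. The total follows as 32 × 1.3 = 41.6, rounded up to 42. The 16 per arm cannot be reproduced, because no standard deviation and no single difference is given. It can only be inverted. With the normal approximation,

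d = (1.960 + 0.842) × √(2/16) = 0.99,

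or 1.02 with the noncentral t distribution. This corresponds to a standard deviation of about 2/0.99 = 2.0 for a 2-point difference and 6/0.99 = 6.1 for a 6-point difference.

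**Step 4. Illustration of dilution.** The assumptions are that 16 per arm gives exactly 80% power, that a fraction f of patients in each arm contributes no treatment difference, and that the standard deviation is unchanged. Then

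power = Φ[(1 − f) × 2.802 − 1.960], and n per arm for 80% power = 16/(1 − f)².

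| f (assumed) | Calculation | Power | n per arm for 80% |
|---|---|---|---|
| 0 | Φ(0.842) | 80% | 16 |
| 10% | Φ(0.561) | 71% | 20 |
| 20% | Φ(0.281) | 61% | 25 |
| 30% | Φ(0.001) | 50% | 33 |

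The noncentral t gives the same rounded powers.

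**Step 5. An alternative illustration.** If a mixed sample left the mean difference intact and only enlarged the standard deviation, by a factor k, then power = Φ(2.802/k − 1.960). For k = 1.10, 1.25 and 1.50 this is 72%, 61% and 46%.

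None of the values of f or k comes from the documents.

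**The case against.** The strongest reply is that the whole article describes an ALS trial, so the phrase in section 1.2 is most plausibly loose drafting. A patient without ALS could not supply the interval to an ALS diagnosis, and staff who know the trial's purpose would probably not enrol one. An article may also leave the diagnostic criteria to the full protocol. Much of this stands: the intent is clearly ALS, and nothing shows that anyone else has been randomised. It does not remove the contradiction. The article does not leave the diagnosis unstated; it states one, and that diagnosis is too broad.

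Several stronger readings are tempting, and the documents do not support them:

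- *That the criterion would enrol patients without ALS.* The text shows only that it could.
- *That every endpoint and the sample size are specific to ALS.* The primary measures in section 1.4.4 (respiratory pressures, cough flow and vital capacities) are general respiratory tests, and section 1.5 does not name ALS. The 0–12 score used for stratification in section 1.3 fits three ALSFRS-R items scored 0–4 (3 × 4 = 12), but that section does not name the scale.
- *That power will fall to 71%, 61% or 50%.* These figures rest on an effect size obtained by inverting the sample size and on assumed fractions. The article gives no decline by diagnosis, so it cannot show that other patients decline more slowly or respond less.
- *That the exclusion of those who "had previous kidney disease or other concomitant diseases" belongs to the same fault.* It pulls in the opposite direction, and its scope is detail that an article can leave to the full protocol. It is no part of this point.

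**Conclusion.** The point holds as an internal contradiction. The stated diagnostic rule in section 1.2 is wider than the population in the title, aim, hypothesis and conclusions, and nothing in the article reconciles them. The firm consequence is that a sample recruited under the literal rule could be mixed, and a mixed sample would not support an ALS-specific conclusion. The effect on power cannot be sized from the documents; the range in the working is an illustration under its stated assumptions and is not evidence of a loss. If all those enrolled have ALS, the trial's results are unaffected and only the wording needs correcting. The correction is worth making now, because the article reports that recruitment, opened in August 2019, is still under way.

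**What to change.** Reword the diagnostic criterion in section 1.2 so that it requires a diagnosis of ALS confirmed by a neurologist at the centre, matching the title and aim. Confirm from existing records that every participant randomised so far has ALS, and report the result. If the check finds a participant without ALS, settle how that participant is handled in the analysis before outcomes are compared between arms.

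The cost is a one-line amendment and a review of the diagnoses already on file, at most 42 participants. No sample-size figure changes as a result.

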### Randomization and allocation

1.3

Following informed consent and all baseline assessments, participants will be randomized 1:1 to either the intervention group (EMT plus breath stacking) or the control group (breath stacking alone-usual care). A stratified block permutation randomization will be used with bulbar and non-bulbar onset symptoms as the stratification factors, to ensure balance between the groups. The patients will be dichotomized into normal to moderate bulbar impairment (score 7–12) and severe bulbar impairment (score 0–6).

The randomization schedule was prepared by a researcher independent of the trial.

The trial is being conducted in accordance with theDeclaration of Helsinki and was approved by the Fundação de Ensino e Pesquisa em Ciências da Saúde (FEPECS) Ethics Committee and received approval 6/18/2019 (Document number 3400412).

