##### Secondary outcomes

1.4.4.4

Data on blood gases will be collected to assess PaCO_2_ levels at baseline. The Amyotrophic Lateral Sclerosis Functional Rating Scale revised score (ALSFR-r), site of onset [bulbar(B) versus non-bulbar (NB)], time elapsed (months) between symptom onset and ALS diagnosis, months elapsed from diagnosis to noninvasive ventilation (NIV) prescription will also be collected. Voice parameters will be assessed by Maximum Phonation Time and its acoustic analysis.

The Functional Oral Intake Scale (FOIS) [19] will be used as an index of daily oral intake. This validated 7-point ordinal scale measures what foods an individual consumes to meet their daily nutritional and hydration requirements and ranges from a 1 (nothing by mouth) to 7 (full oral diet with no restrictions). The Eating Assessment Tool-10 (EAT-10)was administered as a patient reported outcome (PRO) of swallowing function [20]. The EAT-10 is a validated 10-item patient rated questionnaire with each question rated on a 5-point ordinal scale. A total EAT-10 score ranges from 0 (indicative of no self-perceived swallowing impairments) to 40 (indicative of severe swallowing impairments).

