### Statistical analysis

1.6

Baseline characteristics will be summarized, including age, sex, time of diagnosis, onset of symptoms local, drugs, primary and secondary outcomes, and imbalances will be investigated.

For each variable, the Shapiro Wilk test will be used to evaluate the normality of the distribution and the Levene test will be performed to evaluate the homogeneity of variance. The differences between groups will be analyzed by the unpaired *t*-test and for continuous variables and chi-square test for categorical variables. The decline rate will be calculated as the difference between baseline and final observation, dividing the result by the number of months between baseline and last evaluation. Spearman test will be used to evaluate the longitudinal decline correlations between pulmonary function tests and both bulbar impairment and disease progression rate.

Exploratory analysis of 2-year survival will include descriptive Kaplan-Mayer survival curves and cox regression with treatment intent.

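### The role of the bulbar score in the stratification is unclear, and the unpaired t-test leaves out both the stratification factor and baseline as covariates, which may cost power

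*Protocol article*

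**What the plan says.** Randomization and allocation (1.3) gives the design: "A stratified block permutation randomization will be used with bulbar and non-bulbar onset symptoms as the stratification factors". The sentence after it reads: "The patients will be dichotomized into normal to moderate bulbar impairment (score 7–12) and severe bulbar impairment (score 0–6"). It does not say what this split is for. The same section reports that an independent researcher has already prepared the schedule.

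The two classifications are separate variables elsewhere in the article. The score's 0–12 range matches the section on bulbar function (1.4.4.3): "Bulbar function will be assessed using the three components of the revised ALS functional rating scale (ALSFRS-R) relevant to bulbar function", with three items each scored 0–4. Site of onset has its own entry under Secondary outcomes (1.4.4.4): "site of onset [bulbar(B) versus non-bulbar (NB)]".

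Statistical analysis (1.6) fixes the comparison for continuous variables: "The differences between groups will be analyzed by the unpaired" t-test. It names no stratum term and no covariate. The quantity compared is a monthly change: "The decline rate will be calculated as the difference between baseline and final observation, dividing the result by the number of months between baseline and" the last evaluation.

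**The concern.** Site of onset is a fixed fact of history, whereas the score describes current severity. A bulbar-onset patient who scores 9 is bulbar by onset but falls in the normal-to-moderate group by score. A limb-onset patient who scores 5 is non-bulbar by onset but severe by score. Onset alone, score alone, or the two crossed (four strata among 42 patients) would be three different schedules, and the article does not let a reader tell which one was used.

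The analysis does not follow the design. Stratified blocks remove most of the between-stratum variation from the difference between arms. A t-test that ignores the strata still counts that variation in its standard error, so if the stratum predicts decline the interval is wider than it need be. Baseline is a different matter. It is not stratified, so leaving it out as a covariate does not make the standard error wrong; it only forgoes precision. In a trial planned on 16 patients per arm, either loss could matter.

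**Working it through.** **Inputs from the protocol article.** Sample size calculation (1.5): 16 per arm, 80% power, two-sided 5%, 30% attrition, total 42; the effect is given as a range of 2–6% over one year, with no SD. Allocation is 1:1 (1.3).

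**Inputs assumed.** R² (the share of variance in decline explained by the added terms), ρ (the baseline to follow-up correlation), block size and stratum share. The article gives none of these.

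**1. The plan's own figure.** Without an SD, 16 per arm can be turned only into a standardised effect.
- Normal approximation: d = (1.960 + 0.842) × √(2/16) = 0.99.
- Noncentral t with 30 df: d = 1.024. This corresponds to an SD of about 2, 4 or 6 for a difference of 2, 4 or 6%.
- The total follows as 32 × 1.3 = 41.6, that is 42. After 30% loss, 42 × 0.7 = 29.4, so about 29 patients.

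**2. Unadjusted power with 29 patients.** The noncentrality is 1.024 × √(29/4) = 2.76 on 27 df, which gives power of 75.7%.

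**3. Adjustment for stratum and baseline together.** The standard error is multiplied by √(1 − R²). The effect becomes d/√(1 − R²), on 25 df after charging two.

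| Assumed R² | √(1 − R²) | Interval narrower by | d/√(1 − R²) | Power, 29 patients |
|---|---|---|---|---|
| 0 | 1.000 | 0% | 1.02 | 75% |
| 0.10 | 0.949 | 5% | 1.08 | 80% |
| 0.20 | 0.894 | 11% | 1.14 | 84% |
| 0.30 | 0.837 | 16% | 1.22 | 89% |

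The change in the t quantile from 27 to 25 df (2.052 to 2.060) widens each interval by about 0.4%. The narrowing column leaves this out.

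**4. Stratum only, by simulation.** Settings: permuted blocks of 4 within strata, N = 32, 30% of patients in one stratum, 6,000 runs per setting, R² due to the stratum alone.

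| R² | Type I error, t-test | Type I error, stratum in model | Power, t-test | Power, stratum in model |
|---|---|---|---|---|
| 0 | 4.6% | 4.6% | 80% | 79% |
| 0.10 | 3.8% | 4.7% | 81% | 84% |
| 0.20 | 3.1% | 5.5% | 82% | 88% |
| 0.30 | 1.9% | 4.6% | 83% | 91% |

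The t-test falls below its nominal 5% level as the stratum becomes more prognostic. Its power also rises a little, because the design balances the stratum. The gain from modelling the stratum is therefore about 3, 6 and 8 percentage points at R² of 0.10, 0.20 and 0.30, smaller than step 3 alone would suggest.

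**5. Baseline only.** With equal variances at the two times, the standard error of a change score relative to ANCOVA is √(2/(1 + ρ)). This gives 1.15 at ρ = 0.5, 1.05 at 0.8, 1.03 at 0.9 and 1.01 at 0.95. The loss is thus about 1–15%, and small if baseline and follow-up are highly correlated.

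**The case against.** A reader might infer that the stratification factor is defined in two incompatible ways. The text does not go that far. Only onset is called a stratification factor. The score split could be a second factor (the article writes the plural) or a grouping for the planned correlations with bulbar impairment. The fault is ambiguity.

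A reader might also infer that the balanced factor is lost to the analysis. It is not: the schedule exists, and the trial's own analysts can read the factor from it. Readers of the article cannot.

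Nor does the t-test ignore baseline, since the decline rate subtracts it; only the further gain of step 5 is forgone. The argument that the standard error is too large for the design applies to the stratification factor alone.

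The loss is conditional as well. At R² = 0 there is none, and the article leaves the link between bulbar impairment and decline to be tested by Spearman correlation. Starting from 29 evaluable patients is pessimistic. Data collected before withdrawal are kept (Participants, 1.2), and the decline rate uses the last evaluation, so a patient lost after week 8 still contributes. At the same d, unadjusted power is 85% with 36 patients and 90% with all 42.

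Finally, covariates are often left to an analysis plan, and none is shown here. That point carries some weight, but the article does not stay silent: it names a specific test that omits the stratum. These objections limit the size of the point. They leave standing the unexplained score split and the mismatch between design and test.

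**Conclusion.** The point holds as an ambiguity to be reconciled and a conditional loss of efficiency. The article does not say what the bulbar score split is for, and the stated t-test uses neither the stratification factor nor baseline as a covariate. If the stratum is prognostic, the test is conservative: it costs power and does not raise the false-positive rate.

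For an assumed combined R² of 0–30%, intervals would be 0–16% narrower with adjustment. Power with 29 patients would go from about 76% to between 75% and 89%. This rests on an R² the article does not give, on the effect implied by 16 per arm, and on every lost patient having no post-baseline visit. Where the R² comes mainly from the stratum, the power gain is smaller, as the simulation shows. The change is worth making because it costs almost nothing even if the gain turns out to be nil.

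**What to change.** 1. In Randomization and allocation, state which factor or factors the existing schedule uses. State the purpose of the other bulbar split, or say that both define the strata.
2. In Statistical analysis, replace the unpaired t-test for the primary decline-rate comparisons by a linear model (ANCOVA) with arm, the stratification factor or factors actually used, and the baseline value of the outcome.

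The cost is a text correction and two degrees of freedom (one for a single two-level stratification factor, one for baseline), with a third if both splits were used and enter as main effects. No new data are needed, because onset site, bulbar score and baseline outcomes are already collected.
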